## Abstract

**Background:**

Approximately one third of the colorectal cancer survivors (CRCS) experience high levels of psychological distress. Common concerns experienced by CRCS include distress related to physical problems, anxiety, fear of cancer recurrence (FCR) and depressive symptoms. However, psychological interventions for distressed CRCS are scarce. Therefore, a blended therapy was developed, combining face-to-face cognitive behavioral therapy (CBT) with online self-management activities and telephone consultations. The aim of the study is to evaluate the efficacy and cost-effectiveness of this blended therapy in reducing psychological distress in CRCS.

**Methods/design:**

The CORRECT study is a two-arm multicenter randomized controlled trial (RCT). A sample of 160 highly distressed CRCS (a score on the Distress Thermometer of 5 or higher) will be recruited from several hospitals in the Netherlands. CRCS will be randomized to either the intervention condition (blended CBT) or the control condition (care as usual). The blended therapy covers approximately 14 weeks and combines five face-to-face sessions and three telephone consultations with a psychologist, with access to an interactive self-management website. It includes three modules which are individually-tailored to patient concerns and aimed at decreasing: 1) distress caused by physical consequences of CRC, 2) anxiety and FCR, 3) depressive symptoms. Patients can choose between the optional modules. The primary outcome is general distress (Brief Symptom Inventory-18). Secondary outcomes are quality of life and general psychological wellbeing. Assessments will take place at baseline prior to randomization, after 4 and 7 months.

**Discussion:**

Blended CBT is an innovative and promising approach for providing tailored supportive care to reduce high distress in CRCS. If the intervention proves to be effective, an evidence-based intervention will become available for implementation in clinical practice.

**Trial registration:**

This trial is registered in the Netherlands Trial Register (NTR6025) on August 3, 2016.

## Background

Colorectal cancer (CRC) is one of the most frequently diagnosed cancers, with over 3.5 million survivors worldwide [1]. Although the majority of the colorectal cancer survivors (CRCS) are resilient and eventually adjust well, a significant proportion of CRCS experience on-going high levels of chronic distress [2]. The National Comprehensive Cancer Network (NCCN) defines distress as “a multi-factorial unpleasant emotional experience of a psychological (cognitive, behavioral, emotional), social and/or spiritual nature that may interfere with the ability to cope effectively with cancer, its physical symptoms and its treatment. Distress extends along a continuum ranging from common normal feelings of vulnerability, sadness and fears to problems that can become disabling such as depression, anxiety, panic, social isolation and existential and spiritual crisis” [3]. Distress occurs in approximately one third of CRCS [4, 5]. Distress is an unfavorable outcome in itself and a known risk factor for a poor outcome following a cancer diagnosis in the physical, mental and social domains of quality of live (QoL) [6, 7].

The problems related to CRC which underlie distress are very broad. Most previous research has investigated the role of physical, emotional or social problems during the phase of survivorship. A systematic review found that long-term CRCS have good overall QoL [8]. However, the majority of CRCS may still experience problems that can adversely impact upon their daily life. Frequently experienced adverse effects of CRC and its treatment are fatigue [9, 10], pain [11], neuropathy [12], poor body image [13] and gastrointestinal problems [13–15]. A substantial amount of patients will have a permanent stoma after treatment for CRC and may experience ostomy-related problems including gas, constipation, change in clothing, travel difficulties, feeling tired, depressive feelings, and worry about odours and noises [16]. However, there is inconsistent evidence about whether or not there are differences in QoL amongst CRCS with and without a stoma [16, 17]. Sexual dysfunction after CRC treatment is a problem varying between 5 and 88% for men and approximately 50% of the women reported that problem [18].

In addition to distress caused by physical problems, anxiety and depressive symptoms are two major concerns of CRCS. The prevalence of anxiety and depressive symptoms amongst CRCS varies between studies. The reported prevalence of mild to moderate depressive symptoms among CRCS (0–6 years after diagnosis) ranges from 8 to 57% [9, 19–21]. Prevalence rates of mild anxiety in CRCS (0–6 years after diagnosis) vary between 14 and 83% [9, 20, 21]. Moderate levels of anxiety have been reported in 6–68% of CRCS [20, 21]. A specific cancer related fear is the fear of cancer recurrence (FCR), defined as the “fear, worry, or concern relating to the possibility that cancer will come back or progress” [22]. Low to moderate levels of fear can be adaptive, and can motivate appropriate health behavior and surveillance, however moderate to high levels of FCR can have a negative impact on mood, daily functioning and QoL [22]. In a large sample of 10,969 CRCS, 50% of respondents reported fear of their cancer returning [23]. Custers and colleagues [24] found that 38% of the CRCS (*N* = 76) experienced high levels of FCR above a clinically validated cut-off. These high levels of FCR were associated with higher levels of distress, post-traumatic stress and lower QoL. A systematic review of interventions for distress in cancer patients has shown that psychological interventions have small to medium effects on distress levels in cancer patients whereas studies that included specifically participants with high distress showed larger effect sizes [25]. However, most research on distress and psychosocial interventions has been conducted with mixed cancer survivors or breast cancer patients [25]. Due to the prevalence of CRC-related distress, specific physical problems associated with CRC and growing numbers of CRCS, providing interventions for distress in CRCS is of increasing importance.

Relatively few studies have explored the effectiveness of psychological interventions designed to improve emotional outcomes for CRCS. A recent systematic review on psychosocial interventions for CRC patients of all disease stages identified 14 randomized controlled trials RCTs [26]. Only three of these RCTs proved to be effective for different mental health outcomes. These three interventions investigated emotional expression, a progressive muscle relaxation training, and an intervention to enhance self-efficacy. Besides the RCTs described in this systematic review, four other studies were found investigating an intervention specifically for CRCS. Lepore and colleagues [27] tested in a randomized trial whether a home-based expressive writing intervention improved QoL in patients with CRC. The intervention was however not effective. Jefford and colleagues [28] developed an intervention (SurvivorCare) which was nurse-led and consisted of educational materials, needs assessment, survivorship care plan, end-of-treatment session and three follow-up telephone calls. The addition of SurvivorCare to usual care showed no beneficial effect. White and colleagues [29] investigated the effect of a volunteer-delivered telephone-based intervention on reducing anxiety and depression among patients recently diagnosed with CRC. Results indicated no change in depressive symptoms, although there was a reduction in anxiety. Hawkes and colleagues [30] tested another telephone-based intervention which was provided by health coaches and aimed at health behavior change. This intervention improved psychosocial outcomes and QoL, but there was no effect on distress.

To summarize, previous studies on psychological interventions for CRCS are inconsistent with most studies failing to demonstrate a positive effect of the intervention. Most existing studies did not select patients based on distress level [26–29] and therefore might have failed to identify those who might benefit the most from psychological interventions [25]. Furthermore, interventions were either nurse-led [26, 28, 29] or telephone-based [29, 30] which may be less sufficient to improve psychological outcomes compared to psychologist-led interventions. Finally, most intervention studies to date included either only short-term CRCS (< 1 year) or patients who were still during medical treatment [26, 28, 29]. Therefore, treatment efficacy for long-term CRCS is still unclear.

Due to the paucity of evidence-based interventions to reduce psychological distress in CRCS, and the limitations of existing intervention studies, there is an urgent need to develop and evaluate a cost-effective and easily accessible psychological intervention for CRCS. The CORRECT (COloRectal canceR distrEss reduCTion) intervention is a blended therapy to reduce psychological distress amongst CRCS which has been specifically developed to address this need. It is called blended therapy because it is a combination of face-to-face (F2F) cognitive behavioral therapy (CBT), interactive self-management activities at a secure website and telephone consultations. Blended therapy is an innovative and promising approach to psychological care delivery. It reduces therapist workload, and is known to lead to better outcomes and reduced patient dropout compared with internet-only interventions [31–34]. By adding online activities to F2F psychological therapy, patients access treatment at home at their convenience. These online activities consist of homework assignments. Towards the end of the intervention period, self-management is increased through the use of the interactive website. In this way patients take charge of their own health and learn to cope more independently with future challenges. Furthermore, blended therapy provided in the CORRECT intervention is tailored to the needs of each individual. As we know, the CRC population is diverse and includes survivors with a variety of different characteristics and treatments therefore the physical and psychosocial consequences vary between individuals. Distress can be seen as a multi-factorial cluster concept. Despite individual variations in symptom profiles, based on previous research, we know that the most common symptoms in CRCS are distress related to physical consequences, anxiety and depressive symptoms. Therefore, in the present study the intervention is tailored according to individual needs in three optional modules: 1) distress due to physical consequences of CRC, 2) anxiety and FCR, and 3) depressive symptoms. The primary objective of the CORRECT study is to evaluate the efficacy and cost-effectiveness of the CORRECT intervention in decreasing psychological distress in CRCS. A secondary aim is to investigate the usage of online activities at the secure website and how online usage is associated with distress reduction.

## Methods/design

The design, and evaluation of this intervention are in accordance with guidelines of conducting Internet intervention research [35], the CONSORT 2010 statement for parallel group randomized trials [36], and for eHealth interventions [37]. The Medical Ethics Committee of the Radboud university medical center (CMO Arnhem-Nijmegen) (NL55018.091.15) and relevant hospital and institutional human research ethics committees granted ethical approval. The current study is registered in the Netherlands National Trial Register (NTR6025).

### Study design

The CORRECT study is a non-blinded, multicenter randomized controlled, two-arm trial evaluating the efficacy of the CORRECT intervention (blended CBT) compared with care as usual (CAU) in patients who have completed primary curative treatment for CRC. Participants enter the study 6 months to 5 years after completion of primary CRC treatment. After finishing the baseline assessment (T0), participants are randomly assigned to either the intervention or the CAU group. Follow-up assessments are at 4 months (T1) and 7 months (T2) after baseline. CRCS in the intervention group receive the CORRECT-intervention between T0 and T1. The CORRECT study design is summarized in Fig. 1.

**Fig. 1 Fig1:**
[figure not shown]
Study design of the CORRECT-study

### Recruitment and procedure

CRCS are approached for this study from 6 months after completion of medical treatment. Patients are recruited from the Surgery and Oncology Departments of two academic hospitals, Radboud university medical center Nijmegen (Radboudumc) and Amsterdam University Medical Centers (location VUmc), and regional hospitals. Two recruitment methods are employed. Potentially eligible patients are identified retrospectively via hospital registries. They receive mailed invitation letters from their treating physician. Alternatively, patients are prospectively recruited at routine follow-up visits. Treating nurses or physicians invite potentially eligible patients to consider participation, and provide verbal and written information about the study. In both recruitment methods, interested participants are then asked to fill out a participation form allowing contact by the researcher. Patients who do not want to consider participation are asked on voluntary basis to fill out a form containing questions about age, gender and reasons for non-participation. Following receipt of a participation form the researcher sends the patient a secure link to the digital screening questionnaire via e-mail or a hardcopy version via the mail (according to what the patient prefers). After screening, the researcher contacts the patient by phone to address further questions, confirm eligibility criteria and obtain written informed consent. During this telephone screening the researcher checks the self-perceived need for help of a patient with the question whether he/she would have problems worth talking to a psychologist about. After written informed consent, the researcher sends the patient a secure link to the digital baseline questionnaires via e-mail or a hardcopy version via the mail. Randomization occurs after receipt of a completed baseline questionnaire.

### Participant eligibility

CRCS are eligible to participate in this study if they: 1) are 18 years or older; 2) are cancer free at study entry; 3) have completed primary CRC treatment with curative intent (stage I, II or III) between 6 months and 5 years previously; 4) have high distress levels indicated by a score of ≥5 on the Distress Thermometer; 5) have basic Internet skills (e.g. possession of an email address, Internet access at home); 6) are literate in Dutch; and 7) are able to travel to the academic hospital for F2F sessions. Ineligibility criteria include: 1) diagnosis of Lynch Syndrome; 2) active psychotherapeutic treatment at study entry; and 3) inability to provide informed consent due to intellectual disability or cognitive impairment.

### Randomization

Allocation to one of the study conditions is performed using a ratio of 1:1, with blocked randomization, stratified for academic hospital (Radboudumc and VUmc), gender and diagnosis (colon and rectal cancer). Patients are randomly allocated to the CORRECT intervention or CAU with a computer randomization program developed specifically for this study. Two secretaries who are working at one central location in the Radboudumc and who are not involved in the study have access to this program and carry out randomization, thus ensuring the researcher cannot influence allocation sequence. The outcome of randomization is notified by the researcher to the patient via phone and mail.

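### The researcher role that confirms need for help by phone also announces each allocation, so in this open, blocked trial entry decisions can be made with a better-than-chance guess of the arm (low severity)

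*Protocol article*

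**What the plan says.** All references are to the protocol article.

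- **Study design** describes a "non-blinded, multicenter randomized controlled, two-arm trial".
- **Randomization** sets a 1:1 ratio "with blocked randomization, stratified for academic hospital (Radboudumc and VUmc), gender and diagnosis (colon and rectal cancer"). Two secretaries "who are not involved in the study have access to this program and carry out randomization", "thus ensuring the researcher cannot influence allocation sequence". The section ends: "The outcome of randomization is notified by the researcher to the patient via phone and mail".
- **Recruitment and procedure** says that, after the screening questionnaire, "the researcher contacts the patient by phone to address further questions, confirm eligibility criteria and obtain written informed consent". It adds: "During this telephone screening the researcher checks the self-perceived need for help of a patient". The question is whether the patient has problems that merit talking to a psychologist. The baseline questionnaire follows consent, and randomisation follows return of the completed baseline questionnaire.
- **Participant eligibility** lists seven inclusion and three exclusion criteria. Need for help is not among them.
- **Discussion** describes a telephone protocol in which the researcher goes through the completed Distress Thermometer with the patient and confirms orally that psychological help is needed.
- **Developmental process** explains that the check was added after the pilot. Two of the four patients who started treatment there turned out to have no perceived need for help, and one of them left after three appointments.

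**The concern.** Keeping the list away from the researcher protects the sequence from tampering. It does not stop someone who knows the past allocations from forecasting the next one, because blocking forces the arms back into balance. Telling every patient the result gives the researcher role exactly that history. Hospital, gender and diagnosis would ordinarily be known by the time of the call, so the caller would also know which stratum's history applies.

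The forecast matters only if the caller has some discretion over entry. The need-for-help check supplies it: it stands outside the listed criteria, no threshold is stated, and the researcher leads the conversation and draws the conclusion. The pilot suggests that the trait being judged bears on whether patients stay in treatment. If the question were probed differently according to the expected arm, even unconsciously, the arms could differ in motivation and retention. Adjusting for baseline BSI-18 would not reliably remove such a difference. The primary outcome is self-reported by unblinded participants, so protection at entry carries more weight than usual.

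**Working it through.** The plan states no figure for predictability, so there is none to reproduce. The question is how well someone who knows a stratum's allocation history can guess a candidate's arm.

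**Inputs from the article.** The ratio is 1:1 in permuted blocks. There are 2 × 2 × 2 = 8 strata. The total is 160 patients, or 160/8 = 20 per stratum if strata are equal (an assumption).

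**Assumptions.** Block size b is not stated; 2, 4 and 6 are taken as the main range. The guesser picks the arm that is behind in the current block, and tosses a coin when the arms are level.

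**Step 1. No same-stratum patient is randomised between call and allocation.** The chance of a correct guess at each position of a complete block is:

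- b = 2: 1/2, 1. Mean = 1.5/2 = 75%.
- b = 4: 1/2, 2/3, 2/3, 1. Mean = (17/6)/4 = 17/24 = 70.8%.
- b = 6: 0.5, 0.6, 0.6, 0.7, 0.7, 1. Mean = 4.1/6 = 68.3%.

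For example, at position 3 of a block of 4 the first two allocations agree with probability 1/3, and the guess is then certain. Otherwise the arms are level and the guess is a coin toss: 1/3 × 1 + 2/3 × 1/2 = 2/3.

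**Step 2. One same-stratum patient is randomised in between.** The guesser's information is one allocation out of date. Each list moves along by one place: a coin toss enters at the front and the certain last position drops out. Accuracy falls by (1 − 1/2)/b:

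- b = 2: 75% − 25% = 50%.
- b = 4: 70.8% − 12.5% = 58.3%.
- b = 6: 68.3% − 8.3% = 60%.

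**Step 3. Finite strata and other block schemes.** Simulating 160 patients over 8 equally likely strata, with incomplete last blocks and no intervening patient, gives:

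| Blocks | Correct guesses |
|---|---|
| 2 | 74% |
| 4 | 70% |
| 6 | 67% |
| 8 | 65% |
| 10 | 64% |
| Varying, sizes hidden (2/4/6, 4/6, 4/6/8) | 69%, 68%, 67% |

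The small differences from Step 1 come from incomplete blocks. Varying, hidden block sizes do not bring accuracy back to 50% while past allocations are known.

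**Step 4. Certainty.** If the block size is fixed and known to the guesser, the share of allocations fully determined in a complete block with k per arm is (2k/(k+1))/(2k) = 1/(k+1): 50%, 33% and 25% for k = 1, 2, 3. With one intervening patient it falls to 0%, 8% and 8%. If the size is not known, the guesser has better odds but no certainty.

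**Step 5. Role of the strata.** For blocks of 4, accuracy is 70% in 8 strata and 71% in one. Stratification does not raise predictability; the guesser would have to keep eight histories.

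**The case against.** The strongest reply is that the arrangement is conventional. Randomisation is central, by computer, run by uninvolved staff, and takes place only after consent and baseline. The article claims only that the researcher cannot influence the sequence, and that claim is correct. There is no contradiction in the text.

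Timing also counts. The need check comes before consent, dispatch of the baseline questionnaire and its return. According to Assessment, reminders go out only after two weeks, so the gap can run to weeks. Each same-stratum randomisation in that gap makes the history staler, and with blocks of 2 a single one removes the advantage altogether. Against this, about 20 patients per stratum over the whole trial may mean that often nobody intervenes. Accrual speed is not given, so both cases have to be shown.

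The discretion is limited: the distress threshold is patient-rated before the call, and the need question asks for the patient's own view. Some discretion remains, because the Discussion has the researcher confirm the need.

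A reader might go further and infer any of the following, which the article does not support:

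- **The next allocation is known in advance.** That needs a fixed block size known to the researcher, and neither is stated. Leaving this out of an article is normal and is not part of this point.
- **The eight strata make matters worse.** They lower predictability slightly.
- **One individual both screens and announces.** The article names a role, which may be filled by several people across the sites. Nothing in it separates the two tasks, however.
- **Selective enrolment took place.** Nothing shows this.

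**Conclusion.** The point holds as a residual risk of selection bias that follows from a stated procedure rather than from missing detail. The role that confirms an unlisted, partly judged entry condition also receives the allocation history, and the stated safeguard does not cover prediction.

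For assumed blocks of 2, 4 or 6, guess accuracy is at most about 75%, 71% or 67 to 68%, and about 50%, 58 to 59% or 60% once a same-stratum patient intervenes. Simulation error and incomplete blocks account for the one-point ranges. These figures assume that the caller knows and uses the stratum's full history. They measure the opportunity for selection, not bias in the treatment effect, which cannot be derived from the article. Given the interval between call and allocation, the limited discretion and the absence of any sign of selection, severity is low.

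**What to change.** 1. Have the secretaries who run the randomisation also notify the patient and the therapist.
2. Keep allocations from whoever makes the screening calls, as far as practicable, while recruitment is open.
3. Record the patient's answer to the need-for-help question as a fixed yes/no entry criterion before randomisation, and list it with the other criteria.

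This changes no sample size, outcome or analysis. It costs a few minutes of secretarial time per patient, and staff with no study role would have to give the result to distressed patients. Masking may be incomplete in an open trial, since the researcher can still learn arms through later contact such as questionnaire reminders. Item 3 helps even then, because it reduces the discretion on which any guess could act. Varying the block sizes would not be enough on its own.
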